### Sample size

2.8

The null hypothesis of this study is that applying additional T-MSAT to patients with acute LBP will not show any difference in pain between the experimental and control groups. To test this hypothesis, ANCOVA will be used as the primary analysis.

The significance level was set to α=.05 (two-sided test); type 2 error (β) was set to .2; and statistical power was set to 80%. The effect size calculated in a previous study^[16]^ for determining the sample size was .58. When the sample size was calculated based on these parameters, 48 was determined to be the sample size required for each group. Considering that this study will use ANCOVA as the main analysis and the correlation will be set to .5, at least 37 participants would be needed per group.^[34]^ Assuming a drop-out rate of 25%, the goal will be to recruit and enroll a total of 100 participants.

### Patient and public involvement statement

2.9

Neither patients nor the public were involved in the development of the research questions, selection of outcome measures, study design, or study conduct.

### Data management & analysis plan

2.10

#### Data collection and management

2.10.1

This study will use paper case reports and an in-house standard operating procedure (SOP) will be prepared for training the researchers, including assessors and physicians, about case report writing, data input, and treatment procedures. The researchers will enter the data in duplicate. Only the investigator in charge of data management will have access to all the data.

#### Statistical analysis

2.10.2

This study is an RCT on patients with acute LBP caused by a TA, in which we will conduct between-group and within-group comparative analyses on effectiveness and safety indicators obtained from the participants. This study will conduct both intention-to-treat (ITT) and per-protocol (PP) analyses. ITT analysis will be used as the primary analysis, while PP analyses will be performed separately on participants who received 3 or more treatments. Missing values will be processed by multiple imputation as the main method, with the statistics expert blinded. Moreover, last observation carried forward (LOCF) will be used for sensitivity analysis.

The demographic characteristics of the participants and treatment expectancy will be assessed for each group. Continuous variables will be expressed as mean (standard deviation) or median (quartile) and the difference between the 2 groups will be compared by student *t* test. Moreover, categorical variables will be expressed as frequency (%) and tested by Chi-Squared test or Fishers exact test.

The endpoints of this study could be viewed as the amount of change in continuous outcomes (NRS, VAS, ODI, SF-12, aROM, and PCL-5-K) between the baseline and each time point. ANCOVA will be performed as the main analysis, which will use the pre-treatment (baseline) values of each variable and covariant factors selected by group at baseline as covariates, and group as a fixed factor. For additional analysis, a linear mixed model will be used to test the differences in trend changes at each visit. To compare the total amount of each outcome value within the study period for the 2 groups, the areas under the curve for each time point after random allocation will be calculated and compared by student *t* test. In addition, the percentage of patients at time points when NRS and VAS (LBP indicators) decrease by 50% below the baseline will be compared and analyzed. Kaplan–Meier survival analysis will be performed to compare the time required to achieve recovery from LBP, as indicated by pain indicators decreasing by 50% and the curves will be compared by log-rank test. Additionally, Cox proportional hazard model will be used to compare hazard ratios. We also plan to perform subgroup analyses for exploratory purposes, to compare the differences in the level of pain improvement in the T-MSAT and control groups. The significance level for all analyses will be set to .05. SAS 9.4 (© SAS Institute, Inc, Cary, NC, USA) or R studio 1.1.463 (© 2009–2018 RStudio, Inc,Boston, MA, USA) will be used for all statistical analysis and significance will be determined based on *P* < .05.

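### LOCF, the named sensitivity analysis for missing values, does not test missing at random and can mislead, mainly at 12 weeks

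*Protocol article*

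**What the plan says.** Section 2.10.2 (Statistical analysis) fixes two methods for missing data. The first: "Missing values will be processed by multiple imputation as the main method". The second: "last observation carried forward (LOCF) will be used for sensitivity analysis". Neither is limited to a particular outcome or visit, so LOCF would apply to the 12-week scores as well as to D4. The assumption behind the imputation is not stated.

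The same section plans a per-protocol analysis and, as an additional analysis, a linear mixed model for trends. The per-protocol analysis changes who is analysed, not what is assumed about missing values. The mixed model itself relies on missing at random.

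Section 2.8 (Sample size) plans for loss: "Assuming a drop-out rate of 25"%. That rate is not tied to a visit or an arm. Table 2 schedules NRS for low back pain on days 1, 2, 3 and 4, at discharge and at 12 weeks. Section 2.7 puts the primary endpoint at D4. Section 2.4 states that patients cannot be blinded.

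**The concern.** A sensitivity analysis for missing data should show whether the conclusion survives a departure from the assumption of the main analysis. LOCF substitutes a different assumption: no change after the last score. The plan itself expects pain to change. Its primary outcome is a change in NRS, and it analyses time to a 50% fall in pain. A participant who is lost is frozen at an earlier and, on average, worse score, which is then treated as observed.

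If the two arms differ in how many are lost or in how much improvement is forgone, LOCF produces an arm difference that is an artefact, in either direction. Such differences are plausible here. Patients know their allocation, only one arm receives traction and walking with needles in place, and under section 2.12 observation after discontinuation depends on the patient's agreement.

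At stake is how the robustness check is read. LOCF may agree with MI while both are wrong, or disagree when MI is right.

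**Working it through.** **The plan's own figures.** The sample size reproduces. A two-sample t-test with effect size 0.58, two-sided alpha 0.05 and 80% power needs 47.6, so 48 per group, as stated ("48 was determined to be the sample size required for each group"). With correlation 0.5, 48 × (1 − 0.5²) = 36, and one more per group gives 37. Then 37 / (1 − 0.25) = 49.3, so 50 per group and 100 in total. Nothing in this point disputes those numbers.

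**Bias formula.** Let m be the share missing in an arm and g the mean improvement between the last score and the visit analysed. LOCF raises that arm's mean NRS by m × g. For the T-MSAT benefit (control minus T-MSAT):

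bias = (m_control × g_control) − (m_T-MSAT × g_T-MSAT)

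A positive value overstates the benefit. The sign reverses if T-MSAT has the larger product.

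**Size, with the same g in both arms.** The article gives no arm-specific loss and no speed of recovery, so all inputs are assumptions.

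| Visit | Missing, control vs T-MSAT | Forgone improvement (NRS points) | Bias (NRS points) |
|---|---|---|---|
| D4, last score 1–2 days old | 10% vs 5% | 0.5 to 1 | 0.05 × 0.5 = 0.025 to 0.05 × 1 = 0.05 |
| D4, all planned loss already present | 35% vs 15% | 0.5 to 1 | 0.20 × 0.5 = 0.10 to 0.20 × 1 = 0.20 |
| 12 weeks, pain lingers | 35% vs 15% | 0.5 to 1 | 0.10 to 0.20 |
| 12 weeks, in-hospital score carried forward | 35% vs 15% | 2 to 3 | 0.20 × 2 = 0.40 to 0.20 × 3 = 0.60 |

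The 35% and 15% average to the planned 25%.

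**Unequal loss is neither sufficient nor necessary.** Losses of 20% with g = 1.5 and 30% with g = 1.0 give 0.30 − 0.30 = 0. With 25% lost in each arm but g = 2 in T-MSAT and 1 in control, the bias is 0.25 × (1 − 2) = −0.25, so the benefit is understated.

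**Simulation of the mechanism.** Assumptions: ANCOVA, 50 per arm, SD 1.7, correlation 0.5, 2,000 runs. Half of those lost carry the baseline score and half carry the score one visit before the endpoint. In the first three rows loss does not depend on outcome.

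| Scenario (T-MSAT minus control; positive is worse for T-MSAT) | Truth | LOCF | MI |
|---|---|---|---|
| 25% lost in each arm, g = 1.5 | 0 | −0.01, rejects 4.9% | −0.01, rejects 4.6% |
| T-MSAT 35%, control 15%, g = 1.5 | 0 | +0.28, rejects 14.8% | −0.01, rejects 5.3% |
| 25% lost in each arm, true effect | −1.0 | −0.81, power 67% | −1.00, power 81% |
| 25% lost in each arm, T-MSAT dropouts 2 points worse than missing at random predicts | +0.5 | 0.00 | −0.01 |

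The second row agrees with the formula (0.20 × 1.5 = 0.30). These scenarios place the whole planned loss before the endpoint, so they show direction and mechanism rather than the expected size at D4.

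**Does LOCF test missing at random?** In the last row missing at random fails, the true difference is +0.5, and LOCF and MI agree at about zero. Adding 2 points to the imputed T-MSAT values would move the MI estimate by 0.25 × 2 = 0.5, to about 0.49. A delta adjustment shows the departure; LOCF does not.

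**The case against.** The strongest objection is that little may be at risk for the primary endpoint. Patients are in hospital, randomisation is on D2, and NRS is scored daily to D4, so a missing D4 value normally has a predecessor one or two days old. The 25% covers a study that runs to 12 weeks, and stopping treatment does not by itself end observation. This stands, and it is why the D4 figure is small. At an assumed SD of 1.7 to 2, 0.025–0.05 points is 0.0125–0.029 SD, or about 2–5% of the planned effect of 0.58.

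It is also fair that LOCF is supplementary and has no decision role, so it cannot formally overturn the MI result. The raised rejection rates above belong to the LOCF analysis, not to MI. At 12 weeks a telephone interview is allowed, which may limit loss, and NRS at that visit is secondary.

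Three stronger readings are tempting, and the article does not support them:

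- **That LOCF is the only check and missing at random goes untested.** The article names no other missing-data sensitivity analysis, but the full protocol and analysis plan are not shown. What can be criticised is the method it names.
- **That LOCF is biased whenever dropout differs by arm.** The cancelling example disproves this, and bias can also arise with equal dropout.
- **That the condition recovers fast.** The Introduction says such pain can linger. The argument needs only some improvement after the last score.

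Missing at random is likewise inferred as the usual default for MI; the article does not state it.

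**Conclusion.** The point holds as a criticism of a method the article fixes. LOCF is a weak choice of sensitivity analysis: it rests on an implausible assumption, is generally biased when missing share times forgone improvement differs between arms, and does not probe missing at random. The mechanism is certain, but the size depends on assumed inputs.

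At D4 the bias is likely to be negligible, about 0.03–0.05 NRS points, and 0.10–0.20 even if all planned loss had occurred by then. At 12 weeks it could reach 0.4–0.6 points, or 0.1–0.2 if pain lingers. The primary MI estimate and its error rates are unchanged. What is lost is the value of the stated robustness check, mostly for 12-week outcomes. This should be changed, but it does not invalidate the primary analysis.

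**What to change.** In section 2.10.2, replace LOCF, or keep it only as a supplementary display, and name a missing-not-at-random sensitivity analysis built on the planned MI for NRS at D4 and at 12 weeks. Two suitable options, to be used singly or together:

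- **Delta-adjusted tipping point.** Worsen the imputed T-MSAT values by increasing amounts over a range fixed before unblinding, and report the amount at which the conclusion changes. The article gives no basis for a particular range, so the sponsor should justify one.
- **Control-based imputation.** Impute T-MSAT dropouts from the control-arm model.

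The same sentence should state the assumption under which the main imputation is made. The cost is a short text change and a little more programming and reporting. No new data, visits or participants are needed, and the primary analysis stays as it is.

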Among patients hospitalized at Jaseng Hospital of Korean Medicine for injuries caused by a TA, participants for this study will be recruited by posters inside the hospital, the hospital website, and physician recommendations. The recruitment will begin in September 2020.Candidates will listen to an explanation about the study given by the researcher on the first day of hospitalization (D1) and only those who voluntarily agree to participate in the study will fill out an informed consent form. Subsequently, the screening researcher will apply the inclusion and exclusion criteria (Table 1), and only 100 patients who satisfy the criteria will be selected and enrolled in the study.

The participants will be required to complete 6 visits (Vs), including the first day of hospitalization. All surveys will be conducted by face-to-face interview method, except the follow-up (F/U) survey (12 weeks after registration), which may be replaced by a telephone interview. On the second day of hospitalization (D2), the participants will be randomly assigned in a 1:1 ratio to the T-MSAT+IKMT group (N = 50) and IKMT group (N = 50) to undergo treatment. All management of participants and treatment processes will follow the trial protocol.

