#### Experimental group: T-MSAT+IKMT

2.5.1

The T-MSAT+IKMT group will take part in 3 sessions (once a day between D2 and D4). During the 3 sessions of T-MSAT, the group will also take part in IKMT sessions. A doctor of Korean medicine with over 18 months of clinical experience will use a T-MSAT device to apply traction to the patients body, after which needles will be inserted into 6 to 12 acupoints (including BL23, BL54, SP6, GB39, and Ashi acupoints), and the doctor will instruct the patient to walk. The duration of the intervention may be adjusted depending on pain or discomfort felt by the patient.

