### Participants schedule

2.6

This study will be conducted as per the schedule provided in Table 2.

**Table 2 T2:** Schedule of treatment.

	Study period					
	Screening	Active treatment				F/U
Time point	Day 1 of hospitalization	Day 2 (visit 1)	Day 3 (visit 2)	Day 4 (visit 3)	Discharge (visit 4)	12 weeks after registration (visit 5)
Enrollment						
Eligibility screening	○					
Written Informed consent	○					
Sociodemographic characteristics	○					
Information about TA^a^	○					
Medical history (post LBP, and other)	○					
Physical examination	○					
Randomized allocation		○				
Credibility and Expectancy Questionnaire		○				
Intervention						
T-MSAT+IKMT	Δ (only IKMT)	○	○	○	Δ (only IKMT)	
IKMT	○	○	○	○	○	
Assessment						
Check symptoms and Medication change		○	○	○	○	○
NRS of LBP	○	○^∗^	○	○^∗^	○	○
VAS of LBP		○^†^	○	○^†^	○	
ROM of lumbar spine		○^‡^	○	○^‡^	○	
NRS of leg pain		○^§^	○	○^§^	○	○
VAS of leg pain		○^||^	○	○^||^	○	
ODI		○		○^¶^	○	○
SF-12		○		○^¶^	○	○
PGIC				○^¶^	○	○
PCL-5-K		○		○^¶^	○	○
Diagnostic imaging^b^						○
Details of F/U^c^						○
Adverse events		○	○	○	○	○

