### Outcome measures

2.7

The outcomes will be measured at each time point during 12 weeks of the study period, and the primary endpoint is D4 (V3) when the treatment is completed.

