#### Secondary outcomes

2.7.2

Secondary outcomes will be assessed by NRS for radiating leg pain; visual analogue scale (VAS) for lumbar and radiating leg pain; lumbar active range of motion (aROM); Oswestry Disability Index (ODI); 12-item short-form health survey (SF-12); Post-traumatic Stress Disorder Checklist for DSM-5 (PCL-5-K); and Patient Global Impression of Change (PGIC). In addition, F/U investigation will be conducted at 12 weeks after study registration to assess: NRS for leg and LBP; NRS; ODI; SF-12; PCL-5-K; and PGIC, and radiological findings from lumbar imaging performed after TA (L-spine X-ray, L-spine MRI, and L-spine CT) will be recorded, while accident settlement, completion of treatment, and return to work will also be investigated.

VAS for LBP and radiating leg pain: VAS is an assessment tool for recording pain felt by a patient using a line that is 100 mm long, with one end indicating no pain and the other end indicating worst pain imaginable.^[22,24]^ To identify the level of LBP and radiating leg pain felt, the patient will be instructed to indicate a point on the line that best describes his or her level of pain.

NRS of leg pain: The patient will be instructed to select a numerical value between 0 (no pain) and 10 (worst pain imaginable) that best describes the subjective radiating leg pain he or she is feeling.

Lumbar aROM by physical examination: The lumbar aROM that allows the patient to move without pain will be measured. The lumbar aROM in 6 directions (flexion, extension, right lateral flexion, left lateral flexion, right rotation, and left rotation) will be measured.

ODI: The low back functional disability of patient will be assessed using the ODI questionnaire.^[25]^ ODI is a 10-item tool developed for assessing level of low back functional disability, with each item divided into 6 stages and assigned 0 to 5 points. Higher total scores indicate more severe disability and this study will use the official Korean version of the ODI questionnaire.^[26]^

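### For VAS and lumbar aROM the raw AUC ends at a discharge day that differs by patient, so its t test mixes severity with length of stay; none of the AUC comparisons adjusts for baseline

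*Protocol article*

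**What the plan says.** Section 2.10.2 (Statistical analysis) names NRS, VAS, ODI, SF-12, aROM and PCL-5-K as the continuous outcomes. It makes a baseline-adjusted ANCOVA the main analysis and adds a linear mixed model. It then adds an AUC analysis with a stated aim: "To compare the total amount of each outcome value within the study period for the 2 groups". The method is that "the areas under the curve for each time point after random allocation will be calculated and compared by student" t test. No scaling by time, common end day or baseline adjustment is stated for this comparison.

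The visits come from other sections:

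- **Start.** Section 2.2: "On the second day of hospitalization (D2), the participants will be randomly assigned in a 1:1 ratio". T-MSAT is given in "3 sessions (once a day between D2 and D4") (section 2.5.1).
- **Study period.** Section 2.7: "The outcomes will be measured at each time point during 12 weeks of the study period, and the primary endpoint is D4 (V3").
- **Last two visits.** Table 2 lists "Discharge (visit 4") without a calendar day, then "12 weeks after registration (visit 5").
- **Outcomes at week 12.** Section 2.7.2: "F/U investigation will be conducted at 12 weeks after study registration to assess: NRS for leg and LBP; NRS; ODI; SF-12; PCL-5-K" and PGIC. VAS and aROM are not in that list, and their rows in Table 2 end at discharge.

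**The concern.** A raw area under a curve is a level multiplied by a length of time. Two patients' areas compare their levels only if both were observed over the same length. For VAS and aROM they were not, because the last observation falls on whatever day the patient leaves hospital.

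Length of stay arises after randomisation and could respond to treatment, so randomisation does not protect the comparison. If one arm goes home sooner, its VAS area shrinks even when pain is identical. Its aROM area shrinks too, and there a smaller value counts against it. All analyses are judged at P < .05, so such a difference would be reported as a significant effect on pain or mobility. Nor would the area be the 12-week total that the analysis is meant to compare.

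Separately, a t test on the area drops the baseline value that the main analysis uses, although that value is already collected.

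**Working it through.** **Inputs.** From the article: visits on D2, D3, D4, discharge (day d) and 12 weeks; effect size 0.58; correlation .5; two-sided α .05; 50 per arm. Assumed: trapezoid rule (none is named), D1 counted as day 1 so that week 12 is day 85, and d from 5 to 21 (no length of stay is given).

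**Plan's own figures.** The article gives none for the AUC. Its sample size reproduces: the noncentral t at 0.58 gives 47.64, so 48 per group; 48 × (1 − .5²) + 1 = 37; 37/0.75 = 49.3, so 50 per group and 100 in total.

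**1. VAS and aROM: observed length.** The window is d − 2 days.

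| Discharge day | 5 | 7 | 10 | 14 | 21 |
|---|---|---|---|---|---|
| Days in the area | 3 | 5 | 8 | 12 | 19 |

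Constant VAS of 50 mm: 50 × (6 − 2) = 200 mm-days with discharge on day 6; 50 × (12 − 2) = 500 on day 12.

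One falling curve for everyone (assumed: 60 mm on D2, declining about 6% a day): 259.6 mm-days with discharge on day 7, 384.1 on day 10 and 525.2 on day 14. That is +48% from day 7 to day 10 and +37% from day 10 to day 14, with no difference in pain on any given day.

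**2. What this does to the test.** Simulation with identical VAS in both arms (mean 50, SD 20, correlation .5, 50 per arm). Only length of stay differs (SD 3 days, minimum day 5; all assumed).

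| Mean discharge day, arm A vs arm B | Raw AUC t test rejects | Area ÷ days observed rejects |
|---|---|---|
| 9 vs 10 | about 21-22% | about 5% |
| 8 vs 10 | about 67% | about 5% |

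**3. NRS, ODI, SF-12 and PCL-5-K.** The window is 85 − 2 = 83 days for every completer. Only an interior point, discharge, moves. Trapezoid weights are (85 − 4)/2 = 40.5 for discharge and (85 − d)/2 for week 12, so together they carry (166 − d)/166 of the total: 97.0% at d = 5, 94.0% at d = 10, 91.6% at d = 14 and 87.3% at d = 21. D2-D4 is 2/83 = 2.4% of the window.

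**4. Cost of omitting baseline (12-week AUC, d = 8).** Weights for D2, D3, D4, discharge and week 12 are w = (0.5, 1, 2.5, 40.5, 38.5). Assumed effects in SD units are 0, 0.4, 0.58, 0.58 and e, where e is 0 to 0.58. The correlation matrix R has .5 in every off-diagonal cell.

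- Effect on the area: 0.4 + 2.5 × 0.58 + 40.5 × 0.58 + 38.5e = 25.34 + 38.5e, which is 25.34 at e = 0 and 47.67 at e = 0.58.
- Unadjusted variance: w′Rw = 0.5 × 83² + 0.5 × 3130 = 5009.5, SD 70.8.
- Covariance with D2: 0.5 × 83 + 0.5 × 0.5 = 41.75. Adjusted variance: 5009.5 − 41.75² = 3266.4, SD 57.2.

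| Week-12 effect | Standardised effect, t test | Power | Standardised effect, adjusted | Power |
|---|---|---|---|---|
| 0 | 0.36 | 43% | 0.44 | 59% |
| 0.58 | 0.67 | 92% | 0.83 | 98% |

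**The case against.** **The late weighting is what the plan asks for.** A reader might infer that the AUC fails to show the treatment-period effect because discharge and week 12 dominate it. The article does not support that. The stated aim is a total over the study period, which is 12 weeks, and heavy late weight follows from that aim. The D4 effect is covered by the primary ANCOVA. This objection stands.

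**Unequal follow-up is not general.** A reader might extend the length-of-stay problem to all outcomes. It applies only to VAS and aROM, because the others close at a fixed week 12. This also stands.

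**A D2-D4 AUC is not clearly better.** If the week-12 effect is zero, a baseline-adjusted D2-D4 AUC has 88% power, against 43% for the planned AUC. With a persisting week-12 effect of 0.58 SD, the planned AUC has 92%. The ranking turns on a figure the article does not give, and restricting every AUC to D2-D4 would answer a different question.

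**The t test is valid.** Under randomisation, omitting baseline does not bias the comparison when the windows are equal. Only precision is lost.

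**Detail may sit in an SAP that is not shown.** The integration rule and time scaling often do, and the phrase about each time point could mean an area up to each visit. That softens the point but does not remove it. The article already fixes the quantity (a total for each outcome) and the test, and no scaling rule can turn VAS or aROM readings that stop at discharge into a 12-week total.

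**Dependence of discharge on recovery is an inference.** No discharge criterion is given. The length effect itself needs only that discharge days vary; bias between arms needs length of stay to differ by arm.

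**Conclusion.** The point holds for VAS and aROM. As described, their AUC covers a patient-specific length of stay rather than the study period, and a t test on the raw area can signal an effect where none exists. The size depends on how far length of stay differs between arms: in the assumed setting, false rejection is about 21-22% for a one-day difference in mean discharge and 67% for two days. If the arms do not differ in length of stay, there is no bias, only added noise.

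For all AUCs, the missing baseline adjustment is a loss of precision: 43-92% power becomes 59-98% under the effects assumed above, at the protocol's correlation of .5.

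The 12-week AUC for NRS, ODI, SF-12 and PCL-5-K answers its stated question. It should be read knowing that about 87-97% of its weight rests on two visits joined by a straight line. This is an additional analysis, and the primary D4 result does not depend on it.

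**What to change.** 1. For VAS and aROM, analyse the time-averaged AUC (area divided by days observed), or stop at a common day. The last visit on a fixed day for these outcomes is D4, so a common end day without interpolation would be D4, which is a narrower question. Describe the result as an average up to discharge, not as a total over the study period.
2. Keep the 12-week AUC for NRS, ODI, SF-12 and PCL-5-K. State the integration rule and note the share of weight on discharge and week 12.
3. Compare every AUC by ANCOVA adjusted for the pre-treatment D2 value instead of by t test.

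The cost is a change of wording in the analysis plan, with no new data. The downside is small: a time average is no longer a total, and averages over different stays still cover different parts of recovery. On the falling curve above, the average is 259.6/5 = 51.9 mm with discharge on day 7 and 384.1/8 = 48.0 mm on day 10. That is about 8% lower, against 48% higher for the raw area. Reporting length of stay by arm beside the result would let readers judge what remains.
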